## Abstract

**Background:**

The incidence rate of Hashimoto thyroiditis (HT) has gradually increased in recent years. There has been no specific etiological treatment for HT. Even though with normal level of thyroid hormone, the patients may still suffer from various clinical symptoms, such as anterior neck discomfort, fatigue, and mood swings, which seriously impair their quality of life. Acupuncture has long been used in the treatment of thyroid diseases, but there has been no related standardized clinical study as of today. This study aims to assess the feasibility, efficacy, and safety of acupuncture for HT.

**Methods:**

This is a randomized, black-controlled assessor-blinded pilot trial. A total of 60 patients will be recruited and divided into the experimental group (*n* = 30) or the control group (*n* = 30). The experimental group will undergo acupuncture therapy (penetration needling of Hand-Yangming meridian, PNHM) for 16 weeks, followed by a 16-week follow-up period, and the control group will first go through an observation period for 16 weeks, followed by a 16-week compensation PNHM therapy. The primary outcome will be the change of the concentrations of anti-thyroperoxidase antibodies (TPOAb), antithyroglobulin antibodies (TgAb), and thyroid hormone, including total thyroxine (FT_4_), free thyroxine (FT_3_), and thyroid-stimulating hormone (TSH). The secondary outcome measurements include the thyroid-related quality of life questionnaire short-form (ThyPRO-39), The Mos 36-item Short Form Health Survey (SF-36), and Hospital Anxiety and Depression Scale (HAD). Data collection will be performed before the start of the study (the baseline assessment) and at weeks 8, 16, 24, and 32.

**Discussion:**

The study is designed to assess the feasibility and effectiveness of PNHM in reducing the thyroid antibody level and improving the quality of life of HT patients with hypothyroidism or subclinical hypothyroidism. Results of this trial will assist further analyses on whether the acupuncture treatment can alleviate symptoms for patients with HT.

**Trial registration:**

Acupuncture-Moxibustion Clinical Trial Registry AMCTR-IOR-19000308 (ChiCTR1900026830). Registered on 23 October 2019.

## Background

Hashimoto’s thyroiditis (HT), also known as chronic lymphocytic thyroiditis, has become one of the most common endocrine disorders and the most common leading cause of hypothyroidism in recent years, as a result of its gradually increasing incidence rate. The cause of HT is unclear and the diagnoses are mainly based on the positive serum anti-thyroperoxidase antibodies (TPOAb). According to epidemiological studies from different countries, the positive rate of the TPOAb in the population reportedly varies from 8.4 to 17% worldwide [1–4], increasing with age. Among people with elevated TPO antibodies, about 2.5% progress to clinical hypothyroidism each year [5].

HT is a chronic autoimmune disease; after a transient hyperthyroidism that may occur in the early stage, it gradually develops to hypothyroidism in the final stage caused by the autoimmune destruction of the thyroid. Abnormal thyroid function manifests as metabolic abnormalities, thyroid symptoms, and various systemic symptoms. Thyroid symptoms include goiter and anterior neck discomfort. One study stated that the symptom of goiter is not severe in HT patients, but the neck compression symptoms caused by goiter is significant [6]. Systemic symptoms include celiac disease, fatigue, and mood swings [7–9]. The risk of miscarriage and infertility increased in the young women with HT, and thyroid hormone supplementation is not effective in relieving this situation [10]. It was found that HT patients with normal thyroid function may suffer from various clinical symptoms which reduce the quality of life and this may be positively correlated with high thyroid antibody concentrations [11, 12].

It is widely believed that proper intake of nutrients such as iodine, selenium, and iron is beneficial to HT patients [13]. However, there is still no specific etiological treatment for HT. Most studies have mentioned that selenium supplementation can reduce thyroid antibody levels. Although the antibody level is significantly reduced in selenium supplementation, which lasted for more than 3 months, may rebound after the end of treatment [14, 15]. However, some studies have different results that selenium supplementation provides no effect in reducing thyroid antibody level [16–18]. In addition, a gluten-free protein diet may be beneficial for HT patients, but one study stated briefly that this diet plan resulted in a huge impact on the life quality of HT patients more than the disease itself. For the consensus that supplementation of levothyroxine (L-T4) is viable for the treatment of HT patients with subclinical hypothyroidism or clinical hypothyroidism, the starting point and end point of oral thyroid hormone treatment still need confirmation. Some studies indicate that oral thyroid hormone can relieve clinical symptoms of patients when TSH exceeds 10 mIU/l [19]. Different approaches for the treatment of HT require further exploration.

Based on the records from ancient acupuncture books, we find that acupoints on the Yangming meridian have been extensively used in treating various thyroid diseases [20]. Acupoints on the front neck and upper arm, especially at the front edge of the deltoid muscle of the upper arm, were commonly chosen by ancient traditional Chinese medicine (TCM) physicians in the treatment of goiter. This reflects the possible physiological and pathological connection between the thyroid and the upper arms, which further indicates the clinical value of acupuncture on the upper arms in the treatment of thyroid diseases. In modern times, [name], a famous TCM acupuncture physician, is experienced in the treatment of gland diseases of the cervix, including mumps, lymph node tuberculosis, and thyroid disease by applying penetration needling at specific acupoints such as Qu Chi (LI11) and Bi Nao (LI14). Previous studies suggest that acupuncture, as a therapy of complementary and alternative medicine, can bring benefits to patients with thyroid disease [21]. However, there are few randomized controlled trials and few research designs for HT currently. Some important design details in these published studies, such as randomized method and acupuncture scheme, are also insufficient. Therefore, we design the protocol for an RCT to initially explore the feasibility and clinical effectiveness of the treatment of HT with penetration needling of Hand-Yangming meridian (PNHM).

## Methods

### Objective

The objective is to assess the feasibility and effectiveness of PNHM in reducing the thyroid antibody level and improving the life quality of HT patients with hypothyroidism or subclinical hypothyroidism.

### Study design

This study is a randomized, blank-controlled, parallel-group clinical trial. Participants will be assigned to the experimental group or the control group. Study period for both groups lasts for 33 weeks. Eligible participants will be randomly divided into the experimental group and the control group with a ratio of 1:1. The experimental group will undergo acupuncture therapy (PNHM) for 16 weeks, followed by a 16-week follow-up period and the control group will first enter an observation period for 16 weeks, followed by a 16-week compensation acupuncture therapy (PNHM). Assessments will be conducted at baseline and 8, 16, 24, and 32 weeks after randomization. The flowchart is shown in Fig. 1 and the timepoint of assessment is shown in Fig. 2.

**Fig. 1 Fig1:**
[figure not shown]
Trial flow diagram

**Fig. 2 Fig2:**
[figure not shown]
The time point of assessment

### Participants

#### Diagnosis criteria

The diagnosis criteria is a combination of the presence of serum antibodies against thyroid antigens and appearance on thyroid sonogram according to a review and the diagnosis criteria in Chinese clinical guidelines [22, 23]. If thyroid ultrasound indicates diffuse enlargement of the thyroid and reduced echogenicity of glands in a patient with elevated serum thyroid-associated antibody, the clinical diagnosis of HT can be established.

#### Inclusion criteria

Eligible participants should meet the following requirements:
Confirmed clinical diagnosis of Hashimoto’s thyroiditis;Age between 18 and 70 years old;Serum thyroid hormone was within the normal level, and regular administration of exogenous levothyroxine for the past 1 month; andThe informed consent signed.

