### Outcomes and measurements

#### Primary outcomes

The primary outcome will be the change of the concentrations of serum anti-thyroperoxidase antibodies (TPOAb), serum anti-thyroglobulin antibodies (TgAb), and the concentrations of thyroid hormone, including total thyroxine (FT_4_), free thyroxine (FT_3_), and thyroid-stimulating hormone (TSH). Data will be collected before the start of the study (the baseline assessment) and at weeks 8, 16, 24, and 32.

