### Drug combination

The current therapeutic target of HT is to maintain the stability of thyroid function due to the lack of effective treatment for the cause of HT. Therefore, in this study, all participants have been taking exogenous levothyroxine (trade name: Youjiale) to treat hypothyroidism. Considering the influence on serum thyroid-related antibodies, taking medicine that may have an impact on antibodies, such as selenium preparations, will not be allowed. All drugs used by the participants will be recorded in detail, including the drug name, dosage and treatment course, and other information. Clinical researchers will judge the effect of the drug on the study results according to the specific situation.

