## Discussion

The current treatment of HT focuses mainly on the symptom of hypothyroidism that occurs in the later stage of the disease via orally-taken LT4 in a long-term. However, there are not yet any effective treatments for symptoms of neck pressure, fatigue, mood swings, infertility, and others. Comprehensive management methods adopted to delay the progression of the disease or reduce the degree of hypothyroidism deserve further exploration.

Acupuncture has advantages in alleviating clinical symptoms, such as neck pressure, fatigue, and mood swings, and hardly has side effects. Some studies also suggest that acupuncture can stimulate the body to produce a series of neurohumoral immune responses and as a result improve immune disorder state [32]. This suggests that acupuncture has potential therapeutic value for HT. The abovementioned acupuncture treatments can be referred to ancient acupoints for treating thyroid diseases and the experience of modern acupuncture experts. In our earlier clinical observations, this acupuncture method can improve clinical symptoms of HT patients, and some patients’ thyroid-related antibody concentrations have decreased.

Some studies suggest a positive correlation between antibody concentration and the extent of thyroid inflammatory cell infiltration [33, 34]. Thyroid antibody concentrations are also positively correlated with the quality of life of HT patients. Thus, we have chosen antibody concentration as one of the main efficacy indicators to objectively reflect the subject’s immune status. Meanwhile, we will also observe whether the TSH is further stabilized or decreased to the normal range, so as to potentially reduce the dose of FT4 with the help of acupuncture. The use of multiple symptom score scales as secondary efficacy indicators is to fully evaluate the effect of acupuncture treatment on clinical symptoms of HT patients.

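### Entry requires normal thyroid hormone on levothyroxine, yet FT4, FT3 and TSH are primary outcomes, dose change is not analysed, and unblinded staff judge drug effects

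*Protocol article*

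**What the plan says.** All references are to the protocol article.

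- **Inclusion criteria:** "Serum thyroid hormone was within the normal level, and regular administration of exogenous levothyroxine for the past 1 month". TSH is not named here.
- **Primary outcomes:** changes in TPOAb and TgAb "and the concentrations of thyroid hormone, including total thyroxine" (labelled FT4). The list goes on to free thyroxine (labelled FT3) and TSH, so TSH stands under the heading of thyroid hormone. The Abstract has the same list, and Abbreviations repeats the two labels.
- **Objective:** "reducing the thyroid antibody level and improving the life quality of HT patients with hypothyroidism or subclinical hypothyroidism".
- **Discussion:** the team will observe "whether the TSH is further stabilized or decreased to the normal range, so as to potentially reduce the dose of FT4".
- **Drug combination:** all participants take levothyroxine for hypothyroidism. Drug names, dosage and course are recorded. Then: "Clinical researchers will judge the effect of the drug on the study results according to the specific situation".
- **Blinding:** clinical researchers and participants are described as difficult to blind. Only the two data researchers, who collect, keep and analyse the data, are blinded. Under Randomization and allocation concealment, the clinical researcher receives the envelope and learns the allocation.
- **Statistical analysis:** drug dosage is compared between groups at baseline. Paired and independent *t* tests, or their Wilcoxon counterparts, are named for the outcomes.

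**The concern.** Three separate problems meet in the hormone part of the primary outcome.

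First, the entry rule and the hoped-for TSH result do not fit together. A value that is normal at baseline cannot move into the normal range.

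Second, the participants are on replacement therapy, and the Discussion itself names a lower dose as a possible benefit. If doses change during the 16 weeks, the hormone values reflect the dose as well as any effect of acupuncture. Two arms with the same mean TSH on different doses would be reported as showing no difference. A difference in TSH caused by a dose change could be credited to acupuncture.

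Third, the rule for judging drug effects gives discretion to people who know the allocation, with no stated criterion and no stated limit on how the judgement is used. In an open-label comparison with a blank control, such discretion can tilt the result, for the antibodies as well as the hormones.

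In addition, two primary analytes carry names that do not match their symbols, so a reader cannot be sure which assays are meant.

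**Working it through.** **1. Entry rule against the TSH result sought.** There are two readings of the inclusion criterion.

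- *TSH is covered.* This follows the article's own usage, which lists TSH as a thyroid hormone. The number of correctly enrolled participants who can go from abnormal to normal TSH from baseline is then zero, and that part of the Discussion's aim is unavailable.
- *TSH is not covered.* Patients with raised TSH and otherwise normal hormones could enter, and normalization could be shown. This would fit the mention of subclinical hypothyroidism in the Objective, but the text does not say so.

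The article does not settle which reading is meant.

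**2. Share of the primary outcome.** There are five analytes: TPOAb, TgAb, FT4, FT3 and TSH. Three of the five are hormones.

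**3. Can a change within the normal range be seen?** The article gives no SD, target difference or power, so there is no power calculation to reproduce. Its total of 60 is compatible with its own convention: 30 per arm × (1 − 0.20) = 24 completers, inside the stated 20–30.

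Inputs: two-sided alpha 0.05 (Statistical analysis), n = 24 or 30 per arm, and 80% power (my assumption). Normal approximation for two means:

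detectable difference = (1.960 + 0.842) × √(2/n) × SD

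- n = 24: 2.802 × 0.289 = 0.81 SD
- n = 30: 2.802 × 0.258 = 0.72 SD

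To express this against the width W of the normal range, assume that the SD lies between W/6 and W/√12 (the latter is a uniform spread over the range). With n = 24:

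- SD = W/6: 0.809 × 0.167 W = 0.13 W
- SD = W/√12: 0.809 × 0.289 W = 0.23 W

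For change from baseline, multiply by √(2(1 − r)), where r is the correlation with baseline (assumed 0.5 to 0.7). The factor is 1.00 at r = 0.5 and 0.775 at r = 0.7, so the range becomes about 0.10 W to 0.23 W.

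A shift within the range is therefore detectable in principle. The article does not say which such shift would count as a benefit. The tests it names compare location, so more stable TSH would appear in them as no change.

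**4. Where dose enters.** It is recorded (Drug combination), compared at baseline (Statistical analysis), and mentioned as something acupuncture might lower (Discussion). It is not among the primary or secondary outcomes. Week 16 is the last visit before the control group starts its own acupuncture, so baseline to week 16 is the clean window for a comparison by arm.

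**5. Who judges drug effects.** Drug combination gives the task to clinical researchers. Blinding limits blinding to the two data researchers. The judgement is therefore made with the allocation known, although blinded staff who could do the coding already exist.

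**The case against.** The strongest reply is that the Discussion offers two alternatives for TSH, and the first, greater stability, can be assessed in a participant whose TSH is normal. The Objective names antibody level and quality of life, which the two antibodies and the three scales carry. This stands. A reader might infer that the hormone outcomes are incapable of showing the effect sought, but the documents do not support that.

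A reader might also infer that the Objective describes uncontrolled hypothyroid patients, a population the entry rule shuts out. The article never says uncontrolled. Patients with treated hypothyroidism and normal values satisfy the Objective, the Inclusion criteria and Drug combination together. What remains is a matter of wording.

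It is tempting to say that levothyroxine will hold the hormones flat whatever acupuncture does. That presumes dose adjustment during the trial, and the article states no adjustment rule. If doses stay fixed, the hormones could move.

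On drug effects, the article does not say that data will be excluded or altered, and the analysts are blinded. Handling of concomitant drugs is often left to a fuller document. That lowers the certainty of bias. It does not remove the problem, because the article does state a rule, and that rule assigns the judgement to unblinded staff.

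Finally, moving the hormones out of the primary outcome would change a registered pilot that is already enrolling. That is a trade-off for the sponsor, and nothing in the article requires it.

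**Conclusion.** The point holds in a limited form.

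- Three of the five primary analytes are hormones whose values must be normal at entry, if the criterion is read in the article's own terms. On that reading TSH normalization from baseline is impossible for every correctly enrolled participant. If the criterion excludes TSH, this part falls.
- Stability and shifts within the range remain open to study. The detectable shift is about 0.13 W to 0.23 W with 24 completers per arm, on the SD range and 80% power assumed above.
- Hormone results cannot be read with confidence without dose, which the article does not analyse after baseline. The size of any distortion cannot be derived, because the article gives no information on how often or how far doses change.
- The case-by-case judgement by unblinded staff is an avoidable route to bias, also of unknown size.
- The labels for FT4 and FT3 are wrong wherever they are spelled out.

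This is worth amending. It does not undermine the antibody outcomes as such or the trial as a whole.

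**What to change.** 1. **Dose.** Add, as a secondary or supportive analysis, the change in recorded levothyroxine dose from baseline to week 16 by arm, and interpret FT4, FT3 and TSH alongside it.
2. **Drug effects.** Replace the last sentence of Drug combination. All data stay in the main analysis. Drug changes are coded before data lock by the already blinded data researchers, from records that do not reveal the arm. The codes are used only in a sensitivity analysis.
3. **Entry rule.** State whether the thyroid hormone criterion covers TSH, and reconcile the Abstract's discussion paragraph, Objective, Inclusion criteria, Primary outcomes and Discussion accordingly. Which entry or dosing rule should apply is for the investigators, and none is proposed here.
4. **Names.** Correct FT4 to free thyroxine and FT3 to free triiodothyronine in the Abstract, Primary outcomes and Abbreviations, after confirming which assays are run. The Discussion's reference to a dose of FT4 appears to mean levothyroxine and should be corrected too.

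The cost is a small extra analysis and a documented amendment. Drug and dose records and blinded staff already exist. Because the trial is registered and recruiting, the amendment should be dated and the dose analysis labelled as added after enrolment began.

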#### Exclusion criteria

Individuals will be excluded from the study if they meet any of the following criteria:
Thyroid-stimulating hormone receptor antibody (TRAb) positive, and be suspected of combining Graves’ disease or Hashimoto’s hyperthyroidism;Highly suspected thyroid malignancy;Highly suspected subacute thyroiditis;A history of thyroid surgery;Took medicine that may influence antibody concentration (such as selenium supplementation, some Chinese herbal medicine) except for exogenous thyroid hormone in the past 1 month;Severe systemic disease including cardiovascular, cerebrovascular, liver, kidney, and blood system diseases;A history of mental illness;Pregnancy or lactation women;Needle-phobic patients; andExisting local infection or severe skin lesions near the needle site.

#### Withdrawal criteria

Participants will be withdrawn from the study if the following occurs:
Less than 75% of total treatment (i.e., participating in fewer than 36 of the 48 scheduled treatment sessions)Participant’s decision to withdraw from the study at any time for any reason; andOccurrence of any unexpected serious side effects.

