### Sample size estimation

This study aims to evaluate the clinical effectiveness and safety of PNHM for HT. The estimation of sample size should be based on the feasibility, precision about the mean, and variance [24]. It is stipulated that the sample size of exploratory trials is 20–30 per group in China [25]. With consideration of the drop rate of 20% and the feasibility of the study, we finally plan to recruit 60 participants in total to assure the validity of the mean and effect size.

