**Zu San Li (ST36)**	On the anterior aspect of the leg, on the line connecting ST35 with ST41, 3 B-cun inferior to ST35	0.25 × 40 mm	Insert needle perpendicularly to a depth of 1.0–1.5 cun (25.0 mm–37.5 mm). Manipulate needle to get “de-qi” sensation.

Acupoints: San Jian (LI3), He Gu (LI4), Qu Chi (LI11), Bi Nao (LI14), Jian Yu (LI15), Ren Ying (ST9), Zu San Li (ST36). All acupoints are positioned according to the WHO Standard Acupuncture Point Locations in the Western Pacific Region [26].

Needles: “Andy” disposable sterile stainless needles, size of 0.25 × 40 mm and size of 0.30 × 75 mm needles will be used in this trial.

Manipulation: With supine positions, San Jian (LI3) will be penetrated towards He Gu (LI4), Qu Chi (LI11) will be penetrated towards Bi Nao (LI14), Bi Nao (LI14) will be penetrated towards Jian Yu (LI15). Jian Yu (LI15), Ren Ying (ST9), Zu San Li (ST36) will be punctured to standardized needling depths. De-qi sensation (an irradiation feeling deemed to indicate effective needling) should be achieved in each acupoint. Every participant should take three times of treatment per week for 16 weeks, thus a total of 48 treatments, each treatment lasting for 20 min.

Penetration needling is a technique of point-through-point needling. The procedures are as follows: the needle is first being punctured into the skin to a depth of 1–2 mm, then the direction of the needle’s tip is adjusted towards the adjacent acupoint, and finally, the needle is penetrated horizontally within the subcutaneous tissue towards an appropriate depth according to the local anatomical structures.

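### Withdrawing low attenders from the study can remove only acupuncture-arm patients before week 16, so the comparisons with an untreated control are selected on adherence in one arm

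*Protocol article*

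**What the plan says.** The Withdrawal criteria section opens with "Participants will be withdrawn from the study if the following occurs", and its first trigger is "Less than 75% of total treatment (i.e., participating in fewer than 36 of the 48 scheduled treatment sessions". As worded, the participant leaves the study, not just the treatment. The same list contains the participant's own decision to leave, at any time and for any reason.

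The session count comes from the Intervention section: "Every participant should take three times of treatment per week for 16 weeks, thus a total of 48 treatments". The Study design section puts those sessions at different times in the two arms. For the acupuncture arm, "The experimental group will undergo acupuncture therapy (PNHM) for 16 weeks, followed by a 16-week follow-up period". For the other arm, "the control group will first enter an observation period for 16 weeks, followed by a 16-week compensation acupuncture therapy (PNHM". On measurement it says "Assessments will be conducted at baseline and 8, 16, 24, and 32 weeks after randomization".

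The Statistical analysis section plans independent-sample t tests or rank-sum tests between groups, two-sided at 0.05. Nothing in the article says that outcomes are still collected after withdrawal.

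**The concern.** Attendance is observed after randomisation and may be related to outcome. A rule that removes people on attendance, and that can act in only one arm while the control is untreated, leaves a filtered acupuncture group facing a control group that was not filtered in the same way. Randomisation no longer guarantees that the two are comparable, and an unadjusted t or rank-sum test does not restore this.

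The primary outcomes are changes in antibody and thyroid hormone concentrations. If blood samples stop at withdrawal, the missing values cannot be recovered by any analysis set chosen later. The trial also has feasibility as a stated objective, and low attenders are the patients who show how feasible a 48-session course is.

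**Working it through.** **1. The threshold reproduces.** 3 sessions per week × 16 weeks = 48, and 0.75 × 48 = 36. The stated cut-off is arithmetically correct.

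**2. Who can breach the rule, and when.**

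| Period | Acupuncture arm | Control arm | Arm the rule can filter |
|---|---|---|---|
| Weeks 0–16 (assessments at 8 and 16) | 48 sessions scheduled | observation, no sessions | acupuncture only |
| Weeks 16–32 (assessments at 24 and 32) | follow-up, no sessions | 48 compensation sessions | control |

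Weeks 8 and 16 are the only post-baseline assessments with an untreated control, and both fall in the first row.

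**3. How early it can act.** A participant may miss 48 − 36 = 12 sessions. The 13th missed session puts 36 out of reach. At three per week, 13/3 = 4.3, so this can happen in week 5, before the week-8 assessment. The article does not say whether the rule is applied at that point or only at the end of the course.

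**4. Shift in the group difference.** Let p be the share of the acupuncture arm removed. Let D be the mean change from baseline in those retained minus that in those removed, in SD units, positive when attenders do better. The full-arm mean is (1 − p) × retained + p × removed = retained − p × D. The retained mean therefore differs from the full-arm mean by p × D, in the direction of D. The outcome is change from baseline, so D must be a gap in change. A stable difference in level does not by itself produce one.

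**5. Type I error with no true effect.** Inputs are 30 per arm (Abstract), two-sided alpha of 0.05 (Statistical analysis), and assumed p and D. SE = √(1/(30(1 − p)) + 1/30) and z = pD/SE. The rejection rate is Φ(−1.96 + z) + Φ(−1.96 − z).

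| p (assumed) | D (assumed) | n per arm | Shift p × D | SE | z | Type I error |
|---|---|---|---|---|---|---|
| any | 0 | – | 0 | – | 0 | 5% |
| 10% | 0.5 | 27 v 30 | 0.05 SD | 0.265 | 0.19 | 5.4% |
| 20% | 0.5 | 24 v 30 | 0.10 SD | 0.274 | 0.37 | 6.5% |
| 20% | 1.0 | 24 v 30 | 0.20 SD | 0.274 | 0.73 | 11.3% |
| 30% | 1.0 | 21 v 30 | 0.30 SD | 0.285 | 1.05 | 18.4% |

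A simulation of the t test (40,000 runs per row) gave 5.5%, 6.4%, 11% and 19% for the last four rows. With D negative, the error rates are the same but the shift goes against acupuncture. The table assumes that no controls are lost and that removed patients' outcomes are absent from the analysis.

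**The case against.** **The analysis plan may specify intention-to-treat.** It may, and a missing analysis-set definition is not the complaint. The complaint is about a rule the article states in full. An analysis set can only use outcomes that were collected.

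**The rule may be applied at the end of the course.** Then week-8 data would already be in hand and week-16 data would be due, and the article does not say that collected data are discarded. This stands as a limit on the harm. It does not remove it, because the timing is not stated and withdrawal from the study implies that assessments end.

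**A reader might infer that the bias favours acupuncture.** That is plausible if poor attenders do worse: the Adverse events section lists bleeding, hematoma, fainting and serious pain, all possible reasons to miss sessions. But patients may also stop coming because three visits a week are a burden, or because they feel better, and the latter could bias against acupuncture. The document does not link attendance to antibody or hormone change.

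**A reader might infer that adherent patients are compared with all controls.** The text does not support this either, since controls can leave voluntarily, and 16 weeks without treatment may prompt some to do so. What holds is that this particular rule cannot remove them before week 16.

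**Low attenders are still counted.** The number withdrawn under the rule can be reported as an adherence result, so feasibility information is not wholly lost. Their outcomes are.

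**It is a pilot.** The article warns that its results may not show the true effect. It nevertheless plans significance tests between groups.

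**Conclusion.** The point holds as a design fault. Before the last assessment with an untreated control, the attendance rule filters one randomised arm on a post-randomisation variable, and nothing in the article offsets this.

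The size and sign of the bias cannot be derived from the document. Under the assumed values, the shift runs from nothing (D = 0) to 0.30 SD, and type I error from 5% to about 18%. These figures show sensitivity and do not predict what will happen. It would be tempting to read the 20% rows as the plan's own expectation, because the Sample size estimation section says "With consideration of the drop rate of 20% and the feasibility of the study, we finally plan to recruit 60 participants in total". That 20% is a general allowance for dropout, tied neither to this rule nor to one arm, and the document gives no rate for low attendance. The loss of randomisation's protection does not depend on which row is nearest the truth.

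**What to change.** Remove low attendance from the list of reasons for withdrawal from the study. State that participants who attend fewer than 36 sessions remain in all scheduled blood tests and questionnaires unless they withdraw consent, and that they are analysed in the arm to which they were randomised. Keep attendance of at least 36 of 48 sessions for two uses only: to report adherence as a feasibility result, and to define a secondary per-protocol set. The change concerns outcome collection and analysis, and leaves the treatment schedule untouched.

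The cost is a short amendment, with no extra patients or visits beyond those scheduled. Questionnaires are already online, but the primary outcomes need blood samples, so some effort is required to obtain them from people who have stopped attending. The estimate will be somewhat diluted by including low attenders. Recruitment was already under way when the article was written, so the amendment cannot recover outcomes already missed by participants withdrawn before it. Those should be counted and reported by arm.
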